**Primary estimand:**	
Intercurrent events	Early discontinuation of the study
Strategy	Treatment policy
Population-level summary	A Mantel–Haenszel estimate for the risk difference (experimental minus control group) with center as stratification factor will be used to compare treatment failures in all randomized patients
Estimand description	Superiority of the experimental group on the composite endpoint of death, liver transplantation or cholangiosepsis will be measured using the Mantel–Haenszel estimate for the risk difference irrespectively from the early discontinuation of the study
Imputation/data/censoring rule(s)	Patients who early discontinue the study without assessment of the primary endpoint will be counted as treatment failures
Sensitivity analyses	1)Estimation of the risk difference and the corresponding 95% CI without adjustment for center 2)Estimation of the risk difference and the corresponding 95% CI in a model where patients who early discontinue the study without assessment of the primary endpoint are counted as treatment responders 3)Estimation of the risk difference and the corresponding 95% CI in the per-protocol population

#### Analysis of secondary endpoints

All secondary analyses will be exploratory and will be conducted on the ITT population and will be stratified by center.

The single components of the composite primary endpoint will be analyzed in line with the primary analysis using a Mantel–Haenszel estimate for the risk difference.

Necessity of antibiotic treatment, unplanned hospital admission, and ICU admission will be analyzed using a Mantel–Haenszel estimate for the risk difference.

For time to primary endpoint and time to components of the primary endpoint, a Cox regression will be conducted with treatment group and center as independent variables.

The laboratory parameters (bilirubin, alkaline phosphatase, gamma-glutamyltransferase, aspartate aminotransferase, alanine aminotransferase, lactate dehydrogenase, glutamate dehydrogenase, creatinine, albumin, c-reactive protein, cholinesterase, estimated glomerular filtration rate (eGFR) (CKD-EPI formula), and MELD) are assessed with an analysis of covariance (ANCOVA) with change from baseline as dependent variable and treatment, baseline, and center as independent variables.

#### Interim analyses

No interim analyses will be performed.

#### Analysis of safety endpoints

Occurrence of complications and adverse and serious adverse events will be analyzed descriptively using absolute and relative frequencies for the whole population and separately for the experimental and control groups and will be compared with chi-squared tests.

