To date, efficacy of endoscopic interventions has not been proven and an evidence-based standard therapy for SSC–CIP remains to be defined. Programmed (e.g., repeated) ERC interventions are intended to improve biliary drainage, reduce episodes of cholangitis, prevent biliary cirrhosis, and preserve liver function. However, ERC interventions including sphincterotomy and insertion of different catheters and guide wires into the biliary system might on the contrary even be harmful by promoting bacterial cholangitis, hence further accelerating disease progression.

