#### Sample size

The primary aim of the study is to demonstrate superiority of the experimental group compared to the control group in patients with SSC–CIP. The primary endpoint is a failure rate defined as a composite endpoint including liver transplantation, death, or cholangiosepsis after 6 months. Sample size calculation was conducted using a two-group continuity corrected chi-square test in nQuery Advisor 7.0. The type I error is set to 5% (two-sided) and the study aims for a power of 80%. In the present trial, a rate of 70% regarding the composite endpoint is expected in the control group. This assumption is based on the following observations: prognosis of SSC–CIP is dismal with an estimated survival of less than 50% of patients who develop SSC–CIP within 3–6 months [2, 4, 7]. The transplant-free survival of SSC–CIP differs between publications. However, in our large cohort, transplant-free survival was 38.9% at 6 months [9, 16]. Additionally, biliary complications in SSC–CIP are numerous affecting up to 90% of patients [6]. Cholangiosepsis accounts for 20–33% of these biliary complications [6]. A total reduction of 30% is assumed for sample size calculation. This number is estimated from clinical observation and experience of patients with SSC–CIP and PSC [11]. To demonstrate a reduction of the rate from 70 to 40% in the experimental group, a sample size of 49 patients per group is needed leading to *n* = 98 in total. The expected drop-out rate is assumed to be 5% (estimation from clinical practice), which leads to a sample size of 52 patients per study arm and 104 patients in total.

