### Statistical methods

#### Analysis of the primary endpoint

The primary aim of the study is to demonstrate that programmed endoscopic therapy (experimental group) compared to a conservative strategy (control group) reduces the occurrence of treatment failures defined as death or necessity of liver transplantation or development of cholangiosepsis 6 months after randomization.

The primary analysis will be performed according the intention-to-treat (ITT) principle. Specifically, all patients will be analyzed as randomized. The occurrence of the primary endpoint until month 6 will be analyzed by a stratified Mantel–Haenszel estimate for the risk difference (experimental minus control group) with center as stratification factor. If the upper bound of the corresponding 95% confidence interval is below 0, superiority of the experimental group will be concluded. Missing values for the primary endpoint will be counted as treatment failures. Sensitivity analyses will be carried out in the per-protocol population, which consists of all patients who complete the study in accordance to the protocol. According to this, the primary estimand is defined as described in Table 3.

**Table 3 Tab3:** Analysis of the primary endpoint

**Objective:** Demonstrate superiority of programmed endoscopic therapy compared to standard of care on the composite endpoint of all-cause mortality, liver transplantation and cholangiosepsis 6 months after randomization	
**Target population:** Adult patients with by ERC confirmed SSC–CIP	
**Variable/endpoint:** Occurrence of any of the events	

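### For ERC-related and other serious harms outside the secondary endpoints, the plan gives counts and a chi-squared test but no risk difference or confidence interval, unlike benefit

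*Protocol article*

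**What the plan says.** **Harm.** Under Analysis of safety endpoints, complications and (serious) adverse events are described by counts and percentages for all patients and then separately "for the experimental and control groups and will be compared with chi-squared tests". Neither an effect estimate nor an interval is mentioned. The safety population is everyone randomized, analyzed as treated (Analyses populations).

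**Benefit.** The primary endpoint is summarized by a Mantel–Haenszel risk difference, experimental minus control, stratified by center: "If the upper bound of the corresponding 95% confidence interval is below 0, superiority of the experimental group will be concluded".

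**Overlap.** Under Analysis of secondary endpoints, death, liver transplantation, cholangiosepsis, unplanned hospital admission and ICU admission also get a Mantel–Haenszel risk difference, in the ITT population. These match or overlap with five of the safety endpoints in Table 1.

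**What remains.** ERC-related SAEs (including pancreatitis, bleeding, perforation, aspiration pneumonia and sedation reactions), cholangiosepsis-associated septic shock, ACLF and other SAEs have the chi-squared test as their only stated between-arm comparison.

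**The concern.** The trial exists to weigh benefit against possible harm. The background section says that ERC interventions "might on the contrary even be harmful by promoting bacterial cholangitis", the objective is to decide between an endoscopic and a conservative strategy, and the discussion names bleeding, cholangitis and pancreatitis as risks that could be avoided if the result is negative. Several of the harms most specific to the procedure are in the group without an effect estimate.

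In a trial sized for a 30-point difference in a common endpoint, a chi-squared p-value for a much rarer event says little. A non-significant result is compatible both with no excess and with a clinically important one, and the p-value does not distinguish them. A risk difference with its interval does, and it sits on the same scale as the benefit it has to be weighed against.

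**Working it through.** **1. The plan's own figure.** Inputs from Sample size: two-sided 5%, 80% power, 70% versus 40%, continuity-corrected chi-square ("Sample size calculation was conducted using a two-group continuity corrected chi-square test in nQuery Advisor 7.0").

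- Uncorrected: m = [1.960·√(2·0.55·0.45) + 0.842·√(0.7·0.3 + 0.4·0.6)]² / 0.30² = 41.97.
- Corrected: n = (m/4)·[1 + √(1 + 4/(m·0.30))]² = 48.4, so 49 per group.
- Drop-out: 49/0.95 = 51.6, so 52 per group.

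Both stated figures reproduce ("To demonstrate a reduction of the rate from 70 to 40% in the experimental group, a sample size of 49 patients per group is needed"; "which leads to a sample size of 52 patients per study arm and 104 patients in total"). The 80% power applies to the primary endpoint; none is stated for safety.

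**2. Chance that the safety test flags harm.** Assumptions: 52 per arm as treated (no crossover), two-sided 5%, and event rates chosen for illustration. The control arm also has a baseline ERC, stopped after contrast injection, so its rate need not be zero. Method: exact enumeration of two binomials, counting significant results in the direction of harm.

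| Control | Experimental | Excess (points) | Pearson | Yates-corrected |
|---|---|---|---|---|
| 0% | 10% | 10 | 78% | 42% |
| 1% | 10% | 9 | 55% | 30% |
| 2% | 10% | 8 | 40% | 21% |
| 2% | 12% | 10 | 53% | 34% |
| 5% | 15% | 10 | 40% | 26% |
| 10% | 20% | 10 | 29% | 20% |
| 20% | 30% | 10 | 22% | 15% |
| 5% | 25% | 20 | 85% | 77% |
| 10% | 30% | 20 | 75% | 65% |
| 20% | 40% | 20 | 62% | 52% |

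With Pearson, a 10-point excess over a control rate of 5% to 20% is missed in 60% to 78% of trials. At a 2% control rate, an 8-point excess is missed in 60% and a full 10-point excess in 47%. A 20-point excess is detected more often than not throughout the table. So is 10 points over a zero control rate with Pearson, but not with the Yates correction.

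**3. What the p-value leaves out.** Take 8/52 versus 3/52.

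- Pearson: 104·(8·49 − 3·44)² / (52·52·11·93) = 7,030,400 / 2,766,192 = 2.54, p = 0.11 (Yates p = 0.20).
- Risk difference: 5/52 = +9.6 points.
- Wilson limits: 8.0% to 27.5% for 8/52, and 2.0% to 15.6% for 3/52.
- Newcombe lower limit: 9.6 − √[(15.4 − 8.0)² + (15.6 − 5.8)²] = −2.7 points.
- Newcombe upper limit: 9.6 + √[(27.5 − 15.4)² + (5.8 − 2.0)²] = +22.3 points.

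Miettinen–Nurminen intervals show the same for other counts. For 3 versus 0, p = 0.08 and the interval is −1.4 to +15.7 points. For 7 versus 2, p = 0.08 and the interval is −1.5 to +22.1 points.

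**4. Sensitivity to the test variant.** For 5 versus 0 (expected count 2.5 per arm), p is 0.022 with Pearson, 0.067 with Yates and 0.057 with Fisher. A significance verdict on sparse events therefore depends on a choice the safety section does not state.

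**5. Does the interval add power?** No. At 15% versus 5%, the Newcombe interval excludes zero in 36% of trials, against 40% for Pearson.

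**The case against.** Much of the opposing case stands.

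- A reader might infer that harm is compared only through p-values. The documents do not support that. Counts and percentages by arm are planned, so a difference can be obtained by subtraction, and five harm-relevant outcomes get Mantel–Haenszel risk differences. One of them is cholangiosepsis, the serious form of the harm the background section fears most.
- A reader might infer that any large excess would usually go undetected. That depends on event rates the article does not give. It fails for a 20-point excess and, with Pearson, for 10 points over a control rate near zero. A low control rate is plausible, because control patients have one planned diagnostic ERC against repeated therapeutic ones.
- A reader might infer that the investigators intend to treat non-significance as evidence of safety. Nothing in the article says so. A DSMB and three-monthly SAE reports to the ethics committee also stand behind the safety judgement.
- The low power comes from the sample size, not from the safety section, and an interval does not cure it.
- Intervals for safety tables are often left to the analysis plan, which is not shown. But the article does not simply leave the comparison open. It names one, and that stated choice is the weaker summary for sparse events. Nothing in it prevents intervals from being added.

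**Conclusion.** The point holds for a limited set of endpoints: ERC-related SAEs, cholangiosepsis-associated septic shock, ACLF and other SAEs. For these, the stated between-arm comparison is a chi-squared test without an effect estimate or interval, while benefit is reported as a risk difference with an interval.

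At 52 per arm, moderate excesses would often be non-significant, and the p-value would not show that an excess of 15 to 20 points or more can remain compatible with the data. The size of this problem rests on assumed event rates, on no crossover between arms and on the uncorrected test; the Yates form misses more. It is a weakness in reporting, inexpensive to repair. It does not make the chi-squared test invalid and does not affect the primary analysis.

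**What to change.** In Analysis of safety endpoints, keep the counts and percentages. For the endpoints not covered by the secondary analyses, add the risk difference (experimental minus control) in patients with at least one event, with a 95% score-type confidence interval (Miettinen–Nurminen or Newcombe). Make this the main between-arm summary, in place of the chi-squared p-value or alongside it. State that a non-significant difference will not be interpreted as absence of harm. If the statistical analysis plan already provides such intervals, the protocol text only needs to be aligned with it.

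Cost: one sentence in the text and one column in the safety tables. No additional patients, data or visits are needed.

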#### Analyses populations

The primary analysis will be conducted on the ITT-population including all patients that have been randomized. Patients will be analyzed as randomized independently of the performed intervention.

The per-protocol (PP)-population comprises all patients that received the randomized group and were complying with the study-protocol until the end of the observational period and particularly remained in the treatment arm they were allocated to by randomization.

Safety population: In the safety population, all patients are analyzed who are randomized. Patients will be analyzed as treated.

### Oversight and monitoring

#### Responsibilities

This study will be conducted in compliance with the ICH GCP guidelines (as far as possible for this kind of study) and the Declaration of Helsinki. Investigators must have sufficient time to conduct the clinical study in compliance with the study protocol. Furthermore, they have to accurately and completely enter study data in the eCRF. Investigators are responsible for obtaining informed consent of the patients as well as for the preparation and maintenance of adequate case files in order to record observations and other data relevant for this clinical study. Besides, they have to file the study-related records in the ISF and have to maintain its actuality. They will permit study-related monitoring visits. The investigator must provide direct access to the study site’s facilities, to source documents, and to all other study documents.

#### Favorable opinion of independent ethics committees

A favorable opinion of the lead Independent Ethics Committee at Hannover Medical School (Ethikkommission Medizinische Hochschule Hannover) has been obtained prior to study initiation (No 10237_BO_S_2022) in March 2022. Additionally, a favorable opinion will be obtained from each of the center specific Ethics Committee prior to initiation of each site. Written, informed consent to participate will be obtained from all participants.

#### Monitoring

Monitoring is performed for reasons of quality assurance and to verify that the study is conducted according to the protocol as well as to legal and regulatory requirements applicable for clinical trials, particularly the International Conference on Harmonisation (ICH) GCP guidelines.

Quality assurance is based on three components: on-site monitoring, central monitoring, and extensive training. All trial-related processes will follow the SOPs of the Zentrum für Klinische Studien (ZKS) of Hannover Medical School. Central monitoring will include a timely query management process based on consistency and plausibility checks automatically generated from the database, combined with a reminder process for missing documentation. A monitoring plan serves as a guiding document and describes quality assurance details including monitoring activities, responsibilities, and processes. The project manager and/or clinical research associate(s) (CRA(s)) prepares the monitoring plan and reconciles with the coordinating investigator and members of the (clinical) project team.

Pre-study visits/video conferences will be performed in each recruiting study site by independent ZKS CRA to initially check on feasibility of the planned project and to clarify study-specific issues. Site initiation visit/video conferences have to be performed in order to instruct the local investigators in the study protocol, further essential study documents, and documentation of data. Monitoring will be performed by CRAs of the ZKS and/or by subcontracted, qualified, and trained freelancer(s) on a regular basis dependent on specific requirements of the individual study centers. During the study, the CRA will visit the investigational site periodically to check the completeness of subject records, accuracy of entries in the eCRF, and adherence to the protocol and to ICH-GCP. Source data verification will be done according to a risk adapted approach to assure high data quality and patient safety. The focus of on-site monitoring will be on the verification of informed consent documents, eligibility criteria, primary endpoint, key secondary endpoints, and safety aspects. Close-out visits will be done at the end of the trial and in case a site will prematurely be closed.

Key study site personnel must be available to assist the CRA during monitoring visits. The investigator must give the CRA access to all relevant source documents to confirm their consistency with the CRF entries. The investigator must maintain source documents for each subject in the study, consisting of case and visit notes containing demographic and medical information, laboratory data, and the results of any other tests or assessments. All entered information in eCRFs must be traceable to these source documents in the subject’s file. Data not requiring a written or electronic record will be defined before study start and will be recorded directly in the eCRFs which will be documented as being the source data. The investigator must also keep the original of the signed informed consent form(s).

#### Record retention

All relevant study-related documents have to be archived for at least 10 years after completion or premature discontinuation of the clinical study. The investigator agrees to keep the ISF, including the identity of all participating patients, all original signed informed consent forms, detailed records of treatment, and all other applicable study-related documents as well as source documents. The records should be retained by the investigator for at least 10 years after completion or premature discontinuation of the clinical study. Source data have to be kept according to national regulations.

#### Insurance

The trial will be covered by a participant insurance in case the trial site (clinic) does not cover the study by its liability insurance (Haftpflichtversicherung). All subjects/legal representatives will be informed about their rights and obligations in regard to insurance policies before participating in the study. A copy of the insurance policies will be handed out to each patient/legal representative.

#### Amendments

Each amendment of essential study documents has to be approved by the study initiators. Favorable opinion of IEC is required for amendments prior to implementation.

#### Dissemination plans

It is anticipated to publish the results of the clinical trial in a scientific medical journal and at national and international meetings. The responsible investigator will designate the first and the last authors of the publication. The order of subsequent authors will be allocated according to the number of patients recruited by each site. Data will be available to investigators upon reasonable request.

The trial was registered at ClinicalTrials.gov (NCT05396755, date of registration: May 31, 2022, last update: May 31, 2022).

## Discussion

To the present time, no adequately powered randomized clinical trial has investigated the effect of programmed ERC interventions on complications and survival in patients with SSC–CIP.

There is no evidence-based standard of care for patients with SSC–CIP. However, based on the phenotypical similarities to patients with PSC, it is believed that similar treatment strategies might be of benefit in SSC–CIP as well. Therapeutically comparable courses are seen in primary sclerosing cholangitis (PSC). Endoscopic treatment of higher-grade strictures provides clinical benefit in PSC with decreased symptoms of pruritus or cholangitis [20]; it has been further shown that regular/scheduled endoscopic therapy of biliary stenosis can lead to a reduction in cholangitis/cholangiosepsis and prolonged transplant-free survival [11].

In contrast, in SSC–CIP, these endpoints after endoscopic interventions, particularly the prolongation of transplant-free survival and reduction of cholangitis/cholangiosepsis, have not been investigated in prospective, randomized controlled studies yet. Endoscopic intervention has already been shown to be associated with lower bilirubin and ALP levels and short-term clinical improvement [2, 4].

On the other hand, if the present study provides negative results, the risk associated to ERCs including the use of radiation as well as the risk of ERC-related complications such as bleeding, cholangitis, and pancreatitis could be avoided in the future in patients with SSC–CIP. The alternative rationale for the conservative strategy without regular endoscopic intervention followed in the treatment of patients in the control arm of the study is to minimize bile duct manipulation to prevent increasing introduction of multidrug-resistant intestinal bacteria into the biliary system. It has been shown that drug- or multidrug-resistant bacteria and fungal infections are particular risk factors in the bile of SSC patients [21]. It is therefore reasonable to assume that endoscopic manipulation of the biliary tract system could further exacerbate a corresponding burden of non-physiologic microbiota in the bile duct system.

Therefore, the study data that will be collected in this study will most likely establish an evidence-based therapeutic strategy in patients with SSC–CIP concerning a potential benefit of regular biliary interventions.

The investigators are convinced that a risk–benefit consideration clearly favors performance of the here proposed clinical trial. Importantly, this is an investigator-initiated trial, funded by the DFG without any competing commercial or financial interests involved.

Furthermore, accompanying systematic and longitudinal biomaterial analysis will most certainly enable highly stimulating scientific investigations in the field of SSC–CIP related research.

